### Sites and recruitment

At least 20 Brazilian and 2 Colombian ICUs. The expected recruitment rate is 1 patient/month/site. The planned trial duration is estimated at 2.5 years.

### Inclusion and exclusion criteria

Patients must be ≥ 18 years old, with moderate or severe acute respiratory distress syndrome due to CAP and receiving mechanical ventilation. The eligibility criteria are detailed in table 2. The patient flowchart is detailed in figure 1.

**Table 2 t2:** Eligibility criteria

Inclusion criteria	Exclusion criteria
Patients with community acquired pneumonia on invasive MV (pneumonia must have been the cause for initiation of mechanical ventilation) Acute bilateral infiltrate of nonexclusively cardiogenic origin, at the judgment of the attending physician One of the below: Inspired oxygen fraction above 50% with PEEP of at least 8cmH_2_O to maintain saturation above 93% OR PaO_2_/FiO_2_ < 200 with PEEP > 5cmH_2_O	Patients with inclusion criteria for more than 36 hours Intracranial hypertension or acute neurological disease (stroke, subarachnoid hemorrhage Refusal of the legal representative Patients under 18 years of age Patients considered not to be candidates for measures of full invasive support at the time of randomization, that is, patients who have some clear indication, at the time of randomization, for not instituting other invasive support measures Patient with bronchial fistula or barotrauma Patients with a history of home use of oxygen by chronic respiratory disease

MV - mechanical ventilation; PEEP - positive end-expiration pressure; PaO_2_ - partial pressure of arterial oxygen; FiO_2_ - fraction of inspired oxygen.

Note: Inclusion criterion 3a assumes the need for these parameters to maintain at least 93% oxygen saturation. If the patient is admitted with a high inspired fraction and/or high positive end-expiration pressure, it is recommended, if possible, to try to reduce ventilatory parameters (fraction of inspired oxygen and/or positive end-expiration pressure) to assess the oxygen saturation response before considering this criterion fulfilled.

**Figure 1 f1:**
[figure not shown]
Study flow.

### Study interventions

The study interventions will be performed from Day 0 (randomization) through Day 3. The ventilator procedures are summarized in table 3.

**Table 3 t3:** Study interventions after randomization from D0 to D3

Variable	ARDSnet strategy	STAMINA strategy
Baseline adjustments		
Ventilator mode	Volume assist-control	Volume assist-control
Plateau pressure (cmH_2_O)	≤ 30	≤ 30
Initial tidal volume (mL/kg of predicted body weight)	6 or lower in order to maintain Pplat ≤ 30cmH_2_O	6 or lower in order to maintain Pplat ≤ 30cmH_2_O
Respiratory rate setting needed to achieve pH ≥ 7.2	Up to 35 breaths/minute	Up to 35 breaths/minute
Oxygenation goal	SpO_2_ 90 - 94% and PaO_2_ ≥ 60mmHg	SpO_2_ 90 - 94% and PaO_2_ ≥ 60mmHg
Flow wave format	Descending or squared	Descending or squared
Inspiratory pause	Maximum 0.5 seconds	Maximum 0.5 seconds
Flow (L/minute)	30 - 60	30 - 60
I:E	1:1 - 1:2	1:1 - 1:2
PEEP titration adjustments		
PEEP titration*	Low PEEP - FiO_2_ table	Incremental phase: up to PEEP of 20cmH_2_O Decremental phase: reduction in PEEP in steps of 2cmH_2_O PEEP titrated by best static respiratory system compliance
Peep titration stopping criteria		Peak airway pressure ≥ 40cmH_2_O Pplat pressure ≥ 33cmH_2_O Unstable cardiac arrythmias increase vasopressor dose > 20micg/minute†
Decremental phase		Inspiratory pause of 2 seconds at the end of each step to measure compliance value up to PEEP of 8cmH_2_O‡ Best PEEP will be the immediately previous value of a drop in compliance by at least 2mL/cmH_2_O in one decrease or by at least 1mL/cmH_2_O in two sequential decreases‡
Driving pressure	Not allowed to be controlled	Controlled to keep ≤ 14
Additional adjustments	If plateau pressure > 30cmH_2_O: – Reduction of tidal volume up to 4mL/kg of predicted body weight, followed by reduction in PEEP in steps of 2cmH_2_O (if not solved with reduction of TV) – If necessary, is permitted to increase RR up to 40 breaths/minute if pH < 7.2 and PaCO_2_ > 70mmHg with auto PEEP not greater than 2cmH_2_O	If DP > 14 and/or plateau pressure > 30: – Reduction of tidal volume up to 4mL/kg of predicted body weight, followed by reduction in PEEP in steps of 2cmH_2_O (if not solved with reduction of tidal volume) – If necessary, is permitted to increase RR up to 40 breaths/min if pH < 7.2 and PaCO_2_ > 70mmHg with auto PEEP not greater than 2cmH_2_O
Mechanics monitoring	Two times per day apart 8 hours from each assessment	Two times per day apart 8 hours from each assessment
Sedation	Deep sedation with RASS -5 and neuromuscular blockade in the first 72 hours if patient maintains in controlled ventilation. After this time, light sedation (RASS 0 to -2)	Deep sedation with RASS -5 and neuromuscular blockade in the first 72 hours if patient maintains in controlled ventilation. After this time, light sedation (RASS 0 to -2)
New titration procedure in less than 24 hours	Pplat > 30cmH_2_O, change body position (prone or supine), circuit depressurization	Pplat > 30cmH_2_O and/or DP > 14cmH_2_O, change body position (prone or supine), circuit depressurization
Titration routine	D0, D1, D2, D3 24 hours apart and any time if necessary	D0, D1, D2, D3 24 hours apart and anytime if necessary
PEEP weaning after 24 hours with PaO_2_/FiO_2_ ratio > 200	Decrease 2cmH_2_O at 8 hours intervals	Decrease 2cmH_2_O at 8 hours intervals
Ventilation weaning	FiO_2_ ≤ 50% with PEEP ≤ 10cmH_2_O	FiO2 ≤ 50% with PEEP ≤ 10cmH_2_O

Pplat - plateau pressure; SpO_2_ - oxygen saturation; PaO_2_ - partial pressure of arterial oxygen; I:E ratio - ratio of the duration of inspiration to the duration of expiration; PEEP - positive end-expiratory pressure; FiO_2_ - fraction of inspired oxygen; PaCO_2_ - partial pressure of arterial carbon dioxide; DP - driving pressure; RASS - Richmond Agitation-Sedation Scale; RR - respiratory rate.

The predicted weight should be calculated for all patients according to the following formula: men: predicted weight (kg) = 50 + 2.3 {[height (cm) x 0.394] - 60}, women: predicted weight (kg) = 45.5 + 2.3 {[height (cm) x 0.394] - 60}.

* In the STAMINA arm, the titration maneuver can be postponed on a given day if the patient has a PaO2/FiO2 ratio above 200, the plateau pressure is below 30cmH_2_O, the driving pressure is not higher than 14cmH_2_O and the positive end-expiratory pressure is not greater than 10cmH_2_O;

† if any stopping criterion rule is reached, the decremental phase will start from the positive end-expiratory pressure value where the incremental phase stops;

‡ if there is a tie between multiple positive end-expiratory pressure values, the lowest value of positive end-expiratory pressure will be used.

### Intervention group – STAMINA strategy

The STAMINA strategy comprises a DP-limited strategy that includes PEEP titration guided by the best respiratory system compliance. PEEP is titrated as follows: initially, an incremental phase is performed, increasing PEEP up to 20cmH_2_O, respecting the safety stopping criteria detailed in table 3. Nevertheless, in the decremental phase, PEEP is reduced in 2cmH_2_O every one minute and maintained at the level with the best static compliance. Subsequently, the tidal volume and/or PEEP can be adjusted to maintain a DP equal to or lower than 14cmH_2_O and a plateau pressure (Pplat) equal or lower than 30cmH_2_O. A schematic is shown in figure 2.

**Figure 2 f2:**
[figure not shown]
Positive end-expiratory pressure titration - STAMINA strategy.

### Control group – ARDSnet strategy

Positive end-expiratory pressure and fraction of inspired oxygen (FiO_2_) will be adjusted by the low-PEEP ARDSNet table (Table 4) to maintain oxygen saturation (SpO_2)_ between 90% and 94% or a partial pressure of arterial oxygen (PaO_2_) equal to or greater than 60mmHg. Subsequently, the tidal volume and/or PEEP can be adjusted to keep Pplat equal or lower than 30cmH_2_O, regardless of the DP.

**Table 4 t4:** Low positive end-expiratory pressure-fraction of inspired oxygen table

FiO_2_ (%)	30	40	40	50	50	60	70	70	70	80	90	90	90	100
PEEP (cmH_2_O)	5	5	8	8	10	10	10	12	14	14	14	16	18	18 - 24

FiO_2_ - fraction of inspired oxygen; PEEP - positive end-expiratory pressure.

### Sample size

We plan to randomize 500 patients. This number of patients provides a power of at least 90% for detecting a difference of approximately 3 mechanical ventilation-free days and a 5% lower mortality rate in the treatment group.

Considering the raw data from the non-death-related part of the composite outcome (ventilator-free days) and a mortality rate of 60% in the Control group of the CoDEX study^(3)^ as a reference, our simulations reached an average of 4.7 mechanical ventilation-free days in 28 days for the Control group, with quartiles [3.7 - 5.8], standard deviation of 8.2, and a mean of 7.8 mechanical ventilation-free days for the Treatment group, with quartiles [6.5 - 9.2] and a standard deviation of 10.5.

Power estimates were obtained from 2,000 simulations of different scenarios for the primary outcome, considering that death within 28 days would imply zero ventilator-free days, even if the patient was ventilator-free for at least one day during hospitalization. Figure 3 shows the cumulative distribution for the primary outcome from a simulation considering the null model (the effect in the Treatment group was identical to that in the Control group).

**Figure 3 f3:**
[figure not shown]
Cumulative distribution for the number of mechanical ventilator-free days within 28 days. Null scenario.

### Recruitment

Currently, patient enrollment is underway across 29 ICUs throughout Brazil and 2 in Colombia. These centers actively collaborate with the Brazilian Intensive Care Research Network (BRICNet), which has participated in previous studies, ensuring a high standard of patient recruitment and high-quality data. Most of these centers are located in the southern or southeastern region of Brazil, where we expect a higher incidence of community-acquired pneumonia related to higher population density associated with a lower temperature environment during fall and winter.

### Randomization and allocation concealment

The randomization list will be generated electronically using appropriate software. Randomization will be performed in blocks (variable block size) stratified by center and diagnosis of COVID-19. The confidentiality of the randomization list will be maintained through the central automated randomization system via the internet, which is available 24 hours a day (RedCap). The group in which the patient will be allocated will only be disclosed after the information is registered in the electronic system, which will prevent the investigator and the assistant team from predicting the treatment group to which the patient will be allocated. The investigator must visit the website used in the study (RedCap) to formally allocate the patients to the different treatment groups.

### Blinding

There will be no blinding due to the nature of the intervention, which will make it impossible to mask investigators, participants and outcome assessors. However, the outcome assessors only will have access to outcomes data after the end of the study.

### Data collection time sequence

The data that will be collected are specified in table 5 according to figure 4.

**Table 5 t5:** Data collection schedule

	D-1	D0	D1	D2	D3	D28	ICU discharge	Hospital discharge
Eligibility criteria	X							
Randomization		X						
Informed Consent	X							
Time between ICU admission and randomization		X						
Time of MV before randomization		X						
Date of birth		X						
Ventilatory parameters		X	X	X	X			
Arterial blood gas		X	X	X	X			
Sex at birth	X							
Height	X							
Comorbidities	X							
Pneumonia etiology	X							
Vasopressor dose		X	X	X	X	X	X	
RASS at randomization		X						
SAPS 3 parameters		X						
Protocol support: interventions		X	X	X	X			
Prone position		X	X	X	X		X	
Rescue therapies		X	X	X	X		X	
Vasopressors use		X	X	X	X		X	
Creatinine	X	X	X	X	X			
Total bilirubin	X	X	X	X	X			
Date and time of extubation			X	X	X	X	X	
Data and time of reintubation			X	X	X	X	X	
Vital status at ICU discharge						X	X	
Date of death						X	X	X
Number of days in use of MV in hospital						X	X	X
Date of tracheostomy						X	X	X
Data of ICU discharge							X	
Data of hospital discharge								X
Vital status on hospital discharge								X

ICU - intensive care unit; MV - mechanical ventilation; RASS - Richmond Agitation-Sedation Scale; SAPS 3 - Simplified Acute Physiology Score 3.

**Figure 4 f4:**
[figure not shown]
Participant timeline.

### Data collection and management

We will abstract data routinely collected in the intensive care unit through a digital database with easy access via the internet (RedCap).

Several procedures will ensure the quality of the data, including the following:

All researchers will participate in a training session before the beginning of the study to ensure consistency of the study procedures, including data collection.Researchers may call and/or attend brief online meetings with the Study Coordinating Center to resolve issues or problems that may arise, as well as participate in discussion groups by electronic messengers.Data checks to identify inconsistencies will be conducted periodically. Centers will be notified of inconsistencies to provide corrections.The Coordinating Center will review detailed monthly reports on the screening, inclusion, follow-up, consistency, and completeness of the data and will immediately take action to resolve any problems.Site monitoring will be performed during the study for a sample of the sites. Such monitoring will be carried out remotely.

### Statistical analysis

A detailed statistical analysis plan can be found in the Appendix 2 in Supplementary Material. The summarized characteristics of the statistical analysis plan are described below. All analyses will adhere to the principle of a modified intention-to-treat approach. Exclusions of participants after randomization may occur due to refusals, given the retrospective (opt-out) nature of the informed consent. We will evaluate the effect of the STAMINA strategy versus the ARDSNet strategy on the primary outcome using a random ordinal model, with adjustment for baseline age, diagnosis of COVID-19, basal ventilatory ratio, and PEEP. The results will be reported as proportional odds ratio (ORp) with 95% confidence intervals. For binary secondary outcomes, we will compare odds ratios and 95% confidence intervals adjusted for the same variables and used random intercepts at the center. For continuous outcomes, we will present the mean difference and 95% confidence interval.

We will analyze the effect of interventions on the following interest subgroups:

Patients with and without a diagnosis of COVID-19 (confirmed by polymerase chain reaction - PCR);Patients with DP above or below 15cmH_2_O prior to randomization.

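### The primary and mortality models are valid but leave out SAPS 3, which the trial already collects at D0; adding it is a cheap efficiency gain of uncertain size

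*Protocol article*

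**What the plan says.** In the protocol article, Statistical analysis, the effect of the strategy is estimated "on the primary outcome using a random ordinal model". The covariates of that model are given as follows: "with adjustment for baseline age, diagnosis of COVID-19, basal ventilatory ratio, and PEEP". Odds ratios for the binary secondary outcomes are "adjusted for the same variables and used random intercepts at the center". Table 1 shows that these outcomes include in-hospital and ICU mortality within 90 days. The section describes itself as a condensed account: "The summarized characteristics of the statistical analysis plan are described below". The full plan is in Appendix 2, which is not at hand.

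Table 5 (Data collection time sequence) has a row "SAPS 3 parameters", marked in the D0 column.

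The Sample size section plans 500 patients and states "a power of at least 90% for detecting a difference of approximately 3 mechanical ventilation-free days and a 5% lower mortality rate in the treatment" arm. It takes as reference "a mortality rate of 60% in the Control group of the CoDEX study". Death within 28 days is scored as zero days there and in Table 1. The section mentions no covariate in its power simulations.

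**The concern.** With 60% mortality in the control arm and 55% under treatment, most primary outcome values are zeros produced by death. The two leading secondary outcomes are mortality itself. The covariates worth having are therefore those that predict death. Of the four listed, ventilatory ratio and PEEP describe the lungs and the ventilator setting, age is demographic, and COVID-19 is etiological. None measures overall severity of illness, although the trial records a score that does.

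In an ordinal or logistic model, a baseline variable with prognostic value beyond those already included raises the power of the treatment test. It also removes the part of any chance imbalance that it explains. Randomization is stratified by center and COVID-19 only, so severity is balanced by chance alone. What is at stake is precision that could be had without recruiting anyone.

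**Working it through.** **Inputs from the article.** 500 patients; mean (SD) ventilator-free days 4.7 (8.2) control and 7.8 (10.5) treatment; control mortality 60%, treatment taken as 60 − 5 = 55%; death = 0 days.

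**Assumptions.** 1:1 allocation (250 per arm); two-sided alpha 0.05, taken from the 95% intervals; no dropout; no center effect; beta-shaped days among survivors.

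**1. The plan's own figure.** Two-means approximation:
- Pooled SD = √((8.2² + 10.5²)/2) = 9.42; standard error = 9.42 × √(2/250) = 0.843.
- Difference 3.0: 3.0/0.843 − 1.96 = 1.60, power 94.5%. Difference 3.1 (7.8 − 4.7): power 95.7%.
- With SD 10.5 in both arms: 89.2% and 91.0%.

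This agrees with the stated 90% or more.

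**2. Chance imbalance.** The between-arm difference in a standardized baseline score has standard error √(2/250) = 0.089 SD. About one trial in 20 shows a gap above 1.96 × 0.089 = 0.175 SD.

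**3. Outcome distribution for the simulation.** Survivor mean = overall mean/(1 − mortality). Survivor variance = (SD² + mean²)/(1 − mortality) − survivor mean².
- Control: 4.7/0.40 = 11.75 days, SD 9.23.
- Treatment: 7.8/0.45 = 17.33 days, SD 8.93.

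A beta distribution on 0–28 was matched to these moments and rounded to whole days. It returned means 4.70 and 7.80 and SDs 8.20 and 10.51, with 64% and 56% of values at zero (deaths plus survivors rounded to zero).

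**4. Adding a severity covariate.** A standard normal score x was linked to the outcome through a latent value ρx + √(1 − ρ²)·e, mapped to the arm's outcome quantiles. The rank of the outcome was regressed on arm alone, then on arm and x, and results with z > 1.96 were counted (4,000 runs per row). The effective sample size gain is (mean z with x ÷ mean z without x)² − 1. The simulated base model has no other covariates, so ρ must be read as what SAPS 3 adds beyond the four listed ones.

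| ρ (assumed) | AUC for zero days | Power without x | Power with x | Effective sample size gain |
|---|---|---|---|---|
| 0.1 | 0.55 | 79.9% | 79.9% | 0.5% |
| 0.2 | 0.59 | 80.0% | 80.8% | 3% |
| 0.3 | 0.64 | 79.9% | 81.9% | 7% |
| 0.4 | 0.68 | 79.7% | 84.3% | 13% |
| 0.5 | 0.73 | 80.1% | 87.1% | 22% |

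Monte Carlo standard error of one power value: √(0.8 × 0.2/4000) = 0.6 points. On 500 patients, 7% is about 35 and 22% about 110.

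**5. Checks.** Proportional-odds fits on the outcome in eight categories (300 runs; standard error √(0.8 × 0.2/300) = 2.3 points) gave 80% to 81% at ρ = 0.2 and 78% to 86% at ρ = 0.4. When only 70% of treated patients received the treatment distribution, power started near 50% and ended between 50% and 58%.

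The gain in the mortality models was not simulated. Only its direction is argued here.

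**The case against.** The strongest reply is that nothing is wrong. Four prespecified baseline covariates, one of them a stratification factor, give a valid test, and the stated power is not tied to any covariate. That stands, and it limits the point to efficiency.

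The second reply is that the prognostic strength of SAPS 3 appears nowhere in the documents. Only what it adds beyond age, COVID-19, ventilatory ratio and PEEP counts, and at a residual correlation of 0.2 or less that is worth a point of power at most. That also stands, and it is why the range must start at zero.

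Third, the article condenses a plan that is not shown, and a severity-adjusted sensitivity analysis may be there. This carries less weight for the main models: the article names their covariates outright, so the comment is on a stated choice and not on missing detail.

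Fourth, changing a published model late needs care. Under Current trial status, 207 patients had been randomized and the data monitoring committee had already met once. The trial is open-label, D0 is also the first day of intervention, and completeness of SAPS 3 is not reported. These are conditions on the change, not reasons against it.

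A reader might infer from the 80% in the simulation that true power falls short of the stated 90%. The documents do not support that. The 80% depends on an assumed survivor distribution, the inputs to the plan's 2,000 simulations are only partly given, and the two-means calculation reproduces the stated figure.

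**Conclusion.** The point holds as an efficiency recommendation. The listed models are valid but leave out the one general severity score that the trial collects, on outcomes driven mainly by death. Adding it would gain about 0 to 7 points of power on the primary outcome (about 0.5% to 22% in effective sample size) for residual correlations of 0.1 to 0.5. That range is an assumption, and the distributional assumptions listed above also apply. The direction is secure provided SAPS 3 has some residual prognostic value; the size cannot be settled from the documents. It would go too far to read this as a demonstrated loss of power or as a mistake in the plan, because no figure in the article shows either.

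**What to change.** Add SAPS 3 as a continuous covariate, computed from values recorded before the intervention starts, to the primary ordinal model and to the ICU and in-hospital mortality models. Keep age, COVID-19, ventilatory ratio and PEEP. State a simple imputation rule for missing scores. Have the change fixed and dated by people who have not seen comparative data. If Appendix 2 already includes SAPS 3, the article's list should say so.

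The cost is small, since the score is already scheduled. It consists of some overlap with age, possibly some missing scores, and a documented amendment to a published model.

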### Data monitoring

The data monitoring at each site involved in this clinical trial will be carried out by a highly trained and qualified site management team. They will be responsible for conducting planned on-site visits to ensure data accuracy, integrity, and compliance with the study protocol and regulatory requirements. Moreover, the team will meticulously review source documents, case report forms, and other trial-related documents to verify the completeness and quality of the collected data.

### Adverse events

We will collect and review data on suspected unexpected severe adverse events (SAEs). Such events must be reported to the coordinating site within 24 hours. Any SAEs must be reported to the coordinating site within 24 hours. Any SAEs will be managed immediately by the treating team and will be adjudicated by the coordinator center team. Unexpected events will be reported to the research team within 24 hours. It is anticipated that the patient population in the ICU will experience a number of aberrations in laboratory values, signs and symptoms due to the severity of the underlying disease and the impact of standard treatments in the ICU. These events will not necessarily constitute adverse events or SAEs unless they are considered to be related to the study treatment or, in the principal investigator's clinical judgment, are not recognized events consistent with the participants underlying critical illness and/or chronic diseases and the expected clinical course. The main adverse event of interest is barotrauma (pneumothorax, pneumomediastinum, subcutaneous emphysema).

